| Statistical Considerations: | 
DTG + FTC dual therapy is expected to be non- inferior to standard-of-care using a 12% non-inferiority margin assuming that 92% of patients are virologically suppressed at week 48 in the two comparison arms.
 
We will evaluate the proportion of patients with viral suppression at week 48 in each arm, and compute a Mantel-Haenszel risk difference (DTG+FTC minus cART) stratified by monitoring type with a two-sided 95% confidence interval. If the lower confidence limit is higher than -12% we will conclude non-inferiority. If the lower confidence limit is below -12% we will conclude that DTG + FTC is potentially inferior to cART. Per protocol (PP) and intention-to-treat (ITT) analyses will be performed. Exclusion criteria for PP will be: patients who discontinue treatment prematurely for reasons other than death, patients with a treatment adherence of less than 80%, or those who do not have HIV-1 RNA results available at week 48. For ITT analysis, all randomized patients will be analysed in the allocated group regardless of any protocol violations.
 |
| GCP Statement:              | 
This study will be conducted in compliance with the protocol, the current version of the Declaration of Helsinki, the ICH-GCP or ISO EN 14155 (as far as applicable) as well as all national legal and regulatory requirements.
                                                                                                                                                                                                                                                                                                                                                                                                                                                                                                                                                                                                                                                                                                                                                                                                                                                                          |

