### 3.7 Risks / Benefits

The main risk in this trial is virological failure on DTG + FTC dual therapy. In the ART Cohort Collaboration of 18 cohorts from Europe and North America including about 17900 patients, low level viremia measured between 50 and 199 copies/ml was weakly associated with virological failure (aHR 1.38, 95%CI 0.96-2.00) (85). We will measure HIV-1 RNA level in the plasma on a regular basis to monitor for low level viremia. Any patient with HIV-1 RNA  $\geq 100$  copies/ml will undergo an additional HIV-1 RNA measurement 14 days later ( $\pm 5$  days), as well as additional adherence session and review of concomitant medications and dolutegravir and emtricitabine plasma concentration measurements.

We will define virological failure as plasma HIV-1 RNA  $\geq 100$  copies/ml on two consecutive measurements. Any patient reaching virological failure will be assessed for genotypic resistance and pharmacogenetic analyses. This latest analysis will be only done in patients who are included in the SHCS and have also signed a consent form for genetic studies. In case of virological failure, the patient will undergo an additional medical visit with review of adherence, concomitant medications, discussion of results of DTG + FTC plasma concentration. Patients randomised in the DTG + FTC dual therapy arm will be switched to a standard cART regimen while waiting for results of genotypic resistance. Patients randomised in the continuing cART arm will await results of the genotypic results. In both cases, treatment will be adjusted according to genotypic resistance results. All failing patients will complete study procedures until week 48. Figure 3 presents the algorithm for the management of virological failure.

Any patient with HIV-RNA between 20 and 99 copies at any time of scheduled visits will have an additional HIV-RNA measurement after 6 weeks (+/-5 days).

Figure 3: Algorithm for the management of virological failure

[figure not shown]

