## **7.4 Criteria for withdrawal / discontinuation of participants**

Participants will be withdrawn from the trial if:

1. The subject withdraws consent; in this case the patient will continue the antiretroviral treatment with a standard-of-care treatment (cART) and will continue regular follow-up with his/her treating physician;
2. Clinical reasons believed to be life-threatening by the physician, even if not addressed in the toxicity management protocol;
3. Subject is judged by the investigator to be at significant risk of failing to comply with the provisions of the protocol so as to cause harm to self or seriously interfere with the validity of the study result.
4. Study routine procedure must be stopped due to safety concerns.

Withdrawn participants will not be replaced.

Participants in the DTG + FTC dual therapy maintenance arm will discontinue study drugs if (non exhaustive list):

- diagnosed with virological failure defined as plasma HIV-RNA  $\geq 100$  copies/ml on two consecutive occasions;
- become pregnant
- start breastfeeding;
- requiring to use prohibited concomitant medications such as carbamazepine, oxcarbamazepine, phenytoin, phenobarbital, rifampicin or St John's Wort;
- presenting serious adverse events that necessitate to stop dolutegravir and/or emtricitabine;
- reasons related to conceiving and DTG potentially safety issue.

They will still be included in the study, continue their antiretroviral treatment with a standard cART. They can be switched to their previous ARV regimen or to a different one according to the genotypic resistance testing, drug-drug interactions profile and/or clinical evolution, and will complete study procedures until week 48. If the new regimen still fulfills the eligibility criteria the subject can continue the study, otherwise the subject will be withdrawn from the trial. In case of a pregnancy the viral load measurement will be performed once per month accordingly to the EACS guidelines.

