## **11.4 Planned Analyses**

### **11.4.1 Datasets to be Analysed, Analysis Populations**

As recommended by the CONSORT statement (106), two analysis sets will be performed: per-protocol (PP) and intention-to-treat (ITT).

For PP analysis, we will exclude patients for the following reasons: patients who discontinue treatment prematurely (< 47 weeks), unless virological failure occurred before, patients with a treatment adherence of less than 80% while on treatment, those who do not have HIV-1 RNA results at week 48 (+/-21 days), unless virological failure occurred before, or patients with major protocol deviation(s) (i.e. any failure to obtain informed consent, violation of any inclusion criteria, not receiving the allocated treatment or monitoring). Per-protocol and intention-to-treat analyses should reach the same conclusion to consider DTG + FTC as non-inferior to standard treatment.

For ITT analysis, all randomized patients will be analysed in the allocated group regardless of any protocol violations.

All drop outs will be described and reasons for their discontinuation will be given where possible.

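### The synopsis defines the per-protocol set without the virological-failure exception of Section 11.4.1; if followed, it would remove endpoint failures mainly from the DTG+FTC arm

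*Protocol*

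**What the plan says.** The protocol defines the PP set twice.

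- **Synopsis, Statistical Considerations.** "Exclusion criteria for PP will be: patients who discontinue treatment prematurely for reasons other than death". Adherence below 80% also excludes, and the sentence ends "or those who do not have HIV-1 RNA results available at week 48". Death is the only exception named.
- **Section 11.4.1.** It excludes "patients who discontinue treatment prematurely (< 47 weeks), unless virological failure occurred before" and "those who do not have HIV-1 RNA results at week 48 (+/-21 days), unless virological failure occurred before". It also excludes low adherence and major protocol deviations. PP and ITT must reach the same conclusion before DTG+FTC is called non-inferior. The synopsis says both analyses will be done but does not repeat this rule.

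The handling of virological failure (two consecutive HIV-RNA values of at least 100 copies/ml) differs by arm.

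- **Section 7.4.** "Participants in the DTG + FTC dual therapy maintenance arm will discontinue study drugs if" one of the listed events occurs. The first on the list is "diagnosed with virological failure defined as plasma HIV-RNA" at or above that threshold twice in succession. The list covers the DTG+FTC arm only.
- **Section 3.7.** DTG+FTC failures are switched to standard cART while the genotype is pending. By contrast, "Patients randomised in the continuing cART arm will await results of the genotypic results". In both arms treatment is then adjusted to the genotype.

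**The concern.** The two definitions give opposite answers for the patient who matters most to the primary outcome: a DTG+FTC patient with confirmed virological failure who is taken off study drug. Section 11.4.1 keeps that patient in PP as a failure. The synopsis removes the patient as a premature discontinuation.

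The removal is unlikely to be balanced. In the DTG+FTC arm, stopping study drug follows from failure by protocol. In the cART arm it depends on what the genotype shows. A set that excludes patients because of the outcome, and mostly in the experimental arm, shifts the PP difference in favour of DTG+FTC.

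At stake is the purpose of the PP analysis. In a non-inferiority trial it is meant as a second hurdle, and Section 11.4.1 makes it one. A set stripped of failures is hardly a hurdle. The trial is also open-label and HIV-RNA results reach the investigators within a week, so the choice between two definitions should not stay open while outcomes are visible.

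**Working it through.** **1. The plan's own figure.** Inputs from Section 11.2: cART 97%, DTG+FTC 94%, margin 12 points, one-sided alpha 0.025, power 80%.

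n per group = (1.960 + 0.842)² × (0.97×0.03 + 0.94×0.06) / (0.12 − 0.03)² = 7.849 × 0.0855 / 0.0081 = 82.8, so 83. The plan's figure reproduces, and 92 per arm is used below as the recruited size.

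**2. The two PP rules side by side.**

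| Patient | Synopsis | Section 11.4.1 |
|---|---|---|
| Confirmed failure, then study drug stopped | excluded | kept as failure |
| Confirmed failure, then no week-48 HIV-RNA | excluded | kept as failure |
| Stops early without failure | excluded | excluded if before week 47 |

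**3. Effect on the PP difference.** Let f be the share of DTG+FTC endpoint failures that the synopsis rule removes. The documents do not give f, so it is an assumption shown over a range. With true suppression p in the DTG+FTC arm and no cART failure removed:

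expected PP difference = p / (1 − (1 − p)·f) − 0.97

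- At the design values (p = 0.94), 92 × 0.06 = 5.5 DTG+FTC failures are expected. With f = 0.5 about 2.8 leave PP, and the difference moves from −3.0 to 0.94/0.97 − 0.97 = −0.1 points.
- At the margin (p = 0.85), 92 × 0.15 = 13.8 failures are expected. With f = 0.5 about 6.9 leave PP, and the difference moves from −12.0 to 0.85/0.925 − 0.97 = −5.1 points.

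**4. Chance of passing when DTG+FTC is truly worse by exactly the margin.** Model: 92 per arm, binomial outcomes, unstratified Wald 95% interval, lower limit compared with −12 points, no PP exclusions other than those shown. The probabilities come from exact enumeration over both binomials and agree with a 400,000-run simulation where both were run.

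| Share of DTG+FTC failures removed (f) | Expected PP difference, 97% vs 85% | PP alone passes | PP and ITT both pass |
|---|---|---|---|
| 0 (Section 11.4.1) | −12.0 | 3.9% | 3.9% |
| 0.25 | −8.7 | 17% | 3.9% |
| 0.5 | −5.1 | 53% | 3.9% |
| 0.75 | −1.2 | 94% | 3.9% |

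The starting value is 3.9% and not 2.5% because of the Wald approximation at these proportions.

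**5. Sensitivity.**
- The synopsis assumes 92% suppression in both arms. At the margin from there (92% versus 80%), PP alone passes in 3.0% of trials with failures kept and in 53% with f = 0.5.
- If half of the cART failures also leave PP, the 53% at 97% versus 85% becomes 43%. Uneven removal makes the bias worse, but equal shares still weaken PP, because the arm with more failures loses more of them.

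**The case against.** The strongest reply has three parts.

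**Section 11.4.1 is the operative definition and is already right.** The synopsis is a summary, and whoever applies the agreement rule will find it in the same paragraph as the correct PP set. This stands, and it lowers the severity. It does not remove the conflict: the synopsis names an exception of its own (death) and omits the one that matters, so it reads as a different rule and not as a shorter one.

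**ITT protects the claim.** A reader might infer from the PP-alone figures that the trial would falsely declare non-inferiority about half the time. The documents do not support that. ITT keeps every randomised patient, and with the agreement rule the joint rate stays near 4%.

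**The share removed is unknown.** A reader might also infer that every DTG+FTC failure would vanish from PP. That does not follow. Section 5.1 can count a single high value as an endpoint failure, whereas Section 7.4 stops study drug only after two. Unconfirmed failures and those first seen around week 48 would stay in PP. Some cART failures may change regimen after genotyping, and the protocol does not say whether that counts as discontinuation. So removal mainly from the DTG+FTC arm is an inference from the management rules, of unknown size.

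Two further readings of Section 11.4.1 are tempting but weak.
- The 47-week limit might seem to exclude patients whose final visit falls in weeks 45 to 46, inside the ±21-day window. Section 13 ends the study period at the week-48 visit, so such a patient has completed the study and has not naturally stopped early.
- The major-deviation list names inclusion criteria only. This can be read as eligibility in general. Keeping a patient with integrase-inhibitor resistance in PP would, if anything, work against DTG+FTC.

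**Conclusion.** The contradiction is explicit and sits in current text. The synopsis PP rule is wrong as written; the Section 11.4.1 rule is sound. If the synopsis were followed, PP would be biased toward non-inferiority. At the margin, PP alone would pass in about 53% of trials instead of about 4% if half of the DTG+FTC failures were removed (17% for a quarter, 94% for three quarters).

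These figures rest on the assumed share removed, on no cART failure leaving PP, on 92 per arm, and on a simple Wald interval in place of the planned stratified Mantel-Haenszel interval.

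The overall false-claim rate stays near 4% provided that the agreement rule is applied and that failures count as failures in ITT, as Section 5.1 implies. The cost is that PP stops adding protection and that two incompatible definitions of a co-decisive set remain available in an open-label trial. The 47-week limit and the inclusion-criteria wording need only minor clarification.

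**What to change.** 1. Replace the PP sentence in the synopsis with the Section 11.4.1 definition, so that patients with earlier virological failure stay in PP and count as failures, whether they later stop treatment or lack a week-48 HIV-RNA.
2. Repeat in the synopsis that PP and ITT must reach the same conclusion before non-inferiority is claimed.
3. Minor clarifications in Section 11.4.1: state that completing a valid week-48 visit (from week 45) is not premature discontinuation, and name both inclusion and exclusion criteria in the major-deviation list.

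These are wording changes only. They need no new data, no change to patient management and no change to the sample size. They should be made before the analysis sets are fixed.

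### The synopsis and Section 11.4.1 define the per-protocol set incompatibly; applied as written, the synopsis rule would remove confirmed DTG + FTC failures from it

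*Protocol*

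**What the plan says.** Two current passages define the PP set.

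- **Synopsis, Statistical Considerations.** "Exclusion criteria for PP will be: patients who discontinue treatment prematurely for reasons other than death". Two further exclusions follow: adherence below 80%, "or those who do not have HIV-1 RNA results available at week 48". Virological failure is not mentioned.
- **Section 11.4.1.** Excluded are "patients who discontinue treatment prematurely (< 47 weeks), unless virological failure occurred before", patients with adherence below 80% while on treatment, "those who do not have HIV-1 RNA results at week 48 (+/-21 days), unless virological failure occurred before", and patients with major protocol deviations. Death is not mentioned.

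The decision rule stands only in Section 11.4.1: "Per-protocol and intention-to-treat analyses should reach the same conclusion to consider DTG + FTC as non-inferior to standard treatment". The synopsis says only that both analyses will be done. Both texts keep all randomised patients in ITT.

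Two other sections determine who discontinues.

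- **Section 7.4.** "Participants in the DTG + FTC dual therapy maintenance arm will discontinue study drugs if (non exhaustive list" introduces a list whose first item is "diagnosed with virological failure defined as plasma HIV-RNA" at or above 100 copies/ml on two consecutive occasions. The list is written for that arm only. These patients stay in the study and complete its procedures to week 48.
- **Section 3.7.** DTG + FTC failures are switched before the genotype is known. For the other arm, "Patients randomised in the continuing cART arm will await results of the genotypic results". Treatment is then adjusted in both arms according to the genotype.

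**The concern.** Each definition exempts what the other does not. The synopsis keeps deaths and drops virological failures who stop treatment. Section 11.4.1 keeps virological failures and has no death exemption. Nothing in the protocol says which text prevails.

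The difference on virological failure touches the primary outcome. Under the synopsis rule, a DTG + FTC patient with confirmed failure must stop study drug under Section 7.4, counts as a premature discontinuation, and leaves the PP set. The event being tested becomes the reason for exclusion, and the compulsory stop is written for the experimental arm only. A failing cART patient waits for the genotype and may remain in the set as a failure.

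What is at stake is the value of PP as a second, independent test, and the accuracy of the PP estimate that is reported. In an open-label trial, choosing between two written PP definitions after results are known would also be hard to defend.

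**Working it through.** **Step 1: the plan's own figure.** Section 11.2 gives 97% suppression on cART, 94% on DTG + FTC, a 12-point margin, one-sided 0.025 and 80% power.

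n per arm = (1.960 + 0.842)² × (0.97 × 0.03 + 0.94 × 0.06) / (0.12 − 0.03)² = 7.849 × 0.0855 / 0.0081 = 82.85, so 83.

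The stated 83 per group is reproduced. The PP definition does not enter it.

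**Step 2: the two rules side by side.**

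| Patient | Synopsis | Section 11.4.1 |
|---|---|---|
| DTG + FTC, confirmed failure, stops drug under 7.4 | Excluded | Kept as a failure |
| cART, confirmed failure, stays on regimen | Kept as a failure | Kept as a failure |
| cART, confirmed failure, regimen changed after genotype | Excluded if the change counts as discontinuation | Kept as a failure |
| Failure, then no week-48 HIV-RNA | Excluded | Kept as a failure |
| Death, no prior failure, no week-48 HIV-RNA | Exempt by the first clause, excluded by the third | Excluded |
| Week-47 cut-off, major deviations | Not mentioned | Stated |

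The fifth row shows that the synopsis death exemption is largely void, because most patients who die have no week-48 result. It is not wholly void: with a window of ±21 days, a patient could have a valid result and die shortly afterwards.

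**Step 3: expected effect on the PP difference.** Let p be the true suppression rate and s the share of failures removed from an arm. The expected PP proportion is p / [1 − s(1 − p)]. The shares are assumptions.

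*Planned rates (94% versus 97%):*
- None removed: 94.0 − 97.0 = −3.0 points.
- 50% DTG + FTC, 25% cART: 0.94/0.970 − 0.97/0.9925 = 96.9 − 97.7 = −0.8 points.
- 100% DTG + FTC, 0% cART: 100.0 − 97.0 = +3.0 points.

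*At the margin (85% versus 97%):*
- None removed: −12.0 points.
- 50%/25%: 0.85/0.925 − 0.97/0.9925 = 91.9 − 97.7 = −5.8 points.
- 80%/20%: 0.85/0.880 − 0.97/0.994 = 96.6 − 97.6 = −1.0 points.
- 100%/0%: +3.0 points.

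**Step 4: chance that PP concludes non-inferiority when DTG + FTC is truly 12 points worse.** Simulation with at least 200,000 trials, 83 per arm, monitoring strata ignored. The lower limit is d − √[(p₁ − l₁)² + (u₀ − p₀)²], where l₁ and u₀ are Wilson limits. Non-inferiority is concluded if it exceeds −12 points.

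| Failures removed, DTG + FTC / cART | Chance of concluding non-inferiority |
|---|---|
| 0% / 0% (Section 11.4.1) | 2.2% |
| 50% / 50% | 25% |
| 50% / 25% | 31% |
| 50% / 0% | 36% |
| 80% / 20% | 87% |
| 100% / 0% | 100% |

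**Step 5: cross-check.** Exact binomial enumeration with a Wald interval, 92 per arm and no cART failures removed gives 3.9% with failures kept. It gives 17%, 53%, 94% and about 100% when 25%, 50%, 75% and 100% of DTG + FTC failures are removed. The pattern is the same.

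**The case against.** The strongest objection is that the statistical section already has the right rule. A reader might infer that confirmed DTG + FTC failures leave the very set that must confirm non-inferiority. The documents do not support that. The requirement that PP and ITT agree appears only in Section 11.4.1, and the PP set defined in that paragraph keeps patients whose virological failure came first. The stronger reading joins the exclusion rule of one text to the decision rule of the other. This objection stands.

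A reader might also infer that a false claim of non-inferiority could result. It could not rest on PP alone, because ITT keeps every failure under both texts and Section 11.4.1 requires both analyses to agree. This stands too.

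Thirdly, a reader might infer that PP would show non-inferiority whatever the truth, with an estimate of the wrong sign. At the margin, virtual certainty of concluding non-inferiority needs near-complete removal, and the full swing to +3.0 points needs complete one-sided removal. Several things work against that:

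- cART failures may also change regimen after the genotype.
- A single value can fail the primary outcome without two consecutive values at or above 100 copies/ml, and so without triggering the Section 7.4 stop.
- A failure first seen around week 48 would be confirmed after the treatment period.

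At 50%/25% removal the sign is preserved at both sets of rates.

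What the objection does not remove is the contradiction. The synopsis is more than a shortened version of Section 11.4.1, since it contains a death exemption found nowhere else. Nor does the bias need asymmetry: equal removal of half the failures in both arms still raises the 2.2% to 25%.

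**Conclusion.** The concern holds as an internal contradiction. The synopsis and Section 11.4.1 give incompatible PP definitions on virological failure and on death, and one must be chosen before analysis. If the synopsis rule were applied, PP would be biased towards non-inferiority. The chance that it concludes non-inferiority at a true 12-point deficit would rise from 2.2% to about 31%, 87% or 100% at removal shares of 50%/25%, 80%/20% and 100%/0%.

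These figures rest on assumed removal shares, 83 per arm, an unstratified Newcombe interval in place of the stratified Mantel-Haenszel interval, and the reading that a stop under Section 7.4 counts as premature discontinuation. Under Section 11.4.1 the bias does not arise, and ITT is unaffected either way. The loss would be PP as an independent check and an unbiased PP estimate. The point should be corrected, but it does not undermine the trial's decision rule.

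**What to change.** Replace the synopsis PP sentence with the Section 11.4.1 definition, including its exemption for prior virological failure, the 47-week cut-off and the major deviations. Patients who have already failed virologically then stay in PP as failures, even after stopping study drug.

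State one rule for deaths in both places and make it consistent with the week-48 HIV-RNA exclusion: either deaths are kept and also exempted from that exclusion, or they are excluded.

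The cost is wording only. Sample size, study conduct and clinical management do not change. Compared with the synopsis rule, a few more failures stay in PP, so its estimate becomes slightly less favourable to DTG + FTC.
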